## Discussion

EDs are under pressure to provide services for UAU and are potentially significant points of intervention for UAU. Text-messaging interventions have the potential to be a scalable solution that could be used by almost any ED patient and may better support underserved populations. However, little is understood about how to ensure that ED staff systematically offer these products to patients nor how to best engage patients with them during an ED visit. This study will develop and test a comprehensive set of implementation strategies for text-messaging alcohol interventions under “real world” conditions. We will use a deliberative stakeholder-guided intervention mapping procedure to develop the implementation strategy. While applied widely to development of public health interventions, this intervention mapping approach is less frequently used to develop implementation strategies but offers great potential to align the selected implementation strategies and terminology in the implementation science literature, making the strategy more easily replicable for others wishing to use the approach.

In terms of future implications of study findings, as recommended in Pearson et al. [83], the research team and stakeholder group will set a priori criteria to determine whether to progress to a larger scale, fully powered hybrid implementation-effectiveness trial based on preliminary implementation strategy effectiveness in conjunction with feasibility and acceptability [94, 95]. Trial results will be shared with the stakeholder group as well as at scientific conferences and in scientific publications. This larger scale test, if warranted, would expand the number of EDs and the range of implementation outcomes beyond “reach” as well as examine cost-effectiveness of the implementation strategy and effectiveness of the text-messaging intervention in reducing patient alcohol use.

The focus of this study is primarily on studying implementation outcomes, and not patient outcomes; therefore, we will not randomize patients to the text-messaging intervention; instead, all patients will receive the intervention. However, we will collect valuable data from patients to assess feasibility and acceptability of the intervention from their perspective; determine the proportion who engage with the intervention in a real-world situation; examine disparities in gender, race, and ethnicity in enrolled vs. not; and understand why patients enrolled. All of the more than 150 hospitals in New York State are now required by state regulation to screen for substance misuse and such policies are being implemented elsewhere [96]; therefore, findings have the potential to be applied state- and nation-wide and a large number of sites would be available for a larger study.

This project moves forward the implementation science on technology interventions, a fairly new area of research. While the technology focus of this project is on text messaging, findings may be broadly applicable to patient-facing mHealth technologies. Text-messaging interventions have the potential to reach as many patients impacted by UAU as possible, including those traditionally underserved, in a scalable, low-burden manner; this study will illuminate strategies to reach that potential.

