Aim 2: use a stakeholder-engaged intervention mapping process to develop a multi-component implementation strategy for EDs

Aim 3: conduct a mixed method 2-arm cluster randomized pilot study in 4 EDs that serve ~11,000 UAU patients per year to assess the feasibility, acceptability, and preliminary effectiveness of the implementation strategy

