### Aim 3: Examine the feasibility, acceptability, and preliminary effectiveness of the implementation strategy

#### Design

In line with recommendations pertaining to the scope and target outcomes of pilot studies for implementation trials [83–85], the main goal of this pilot trial is to assess the (1) feasibility (i.e., perceptions among ED clinical staff members that the implementation strategy can be successfully used), (2) acceptability (i.e., perceptions among ED clinical staff members that the implementation strategy is agreeable, palatable, or satisfactory), and (3) and preliminary effectiveness of the implementation strategy. We will operationalize our effectiveness outcome as “reach” (i.e., proportion of eligible patients that enroll in the text intervention), which is a key outcome recommended in the implementation science literature [83, 85–87]. The design is a mixed method, two-armed, study in 4 EDs (2 assigned to the new implementation strategy vs. 2 implementation as usual control). Qualitative and quantitative measures will be collected and analyzed simultaneously and merged—qualitative data will provide context to and explanation of the quantitative results in a complimentary way, representing a QUAL + QUAN structure that gives equal emphasis to both types of data [65].

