#### Data sources and measures

##### Effectiveness/reach

Effectiveness will be examined by calculating how many patients were eligible (positive AUDIT-C) based on EHR data and the proportion who enrolled in the intervention as collected by the text platform. Demographics will also be collected from the EHR and text platform to examine differences in characteristics between who was eligible based on AUDIT-C score and who enrolled. In the text platform, each study site will have a unique enrollment text code number, allowing for tracking of patients that enrolled by site and when they enrolled, demographics, and responses to the intervention tailoring questions (e.g., drinking patterns, self-efficacy, motivation). We anticipate there will be ~5000 UAU eligible patients identified during the study trial period based on (1) sites’ current census, (2) current screen positive rates, and (3) screening completion rates based on our previous evaluations in this integrated health system.

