#### Analysis

The same procedures described in aim 1 will be used to analyze qualitative data for aim 3. For the reach/effectiveness quantitative data, we will calculate a proportion for each study condition (e.g., numerator: # of patients in control or intervention sites who enrolled in the intervention; denominator: # of patients with positive AUDIT-C) and use *z*-tests for independent proportions [93] to examine whether control and intervention sites differ significantly. We will also use *z*-tests to examine differences in demographics between those eligible and enrolled to determine whether there are gender or racial disparities. For these proportional analyses [94], to achieve 80% power, a sample size of at least 300 in each condition is needed (total of 600) to detect a 10% difference in proportions with significance level of *p* = .05. For the feasibility/acceptability staff and patient survey data, we will calculate descriptive statistics for each. We will triangulate this quantitative data with the qualitative data by merging the results. No identifying information will be maintained by the study team for any staff or patients; all participants will be identified with a participant ID.

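### Statistical significance of the reach difference between 2 and 2 EDs would be a poor progression criterion, and the plan should exclude it before the criteria are set

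*Protocol article*

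**What the plan says.** The Discussion of the Protocol article says that the research team and stakeholder group "will set a priori criteria to determine whether to progress to a larger scale" trial, and that this will be "based on preliminary implementation strategy effectiveness in conjunction with feasibility and acceptability". No thresholds are given.

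Aim 3, Design, defines effectiveness as reach, the "proportion of eligible patients that enroll in the text intervention", and describes four EDs, "2 assigned to the new implementation strategy vs. 2 implementation as usual control". Aim 3, Analysis, pools patients within each condition and uses a z-test for independent proportions "to examine whether control and intervention sites differ significantly". That is the only between-arm effectiveness analysis stated. The accompanying sample size is 300 patients per condition for 80% power "to detect a 10% difference in proportions".

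Under Feasibility and acceptability, the staff AIM and FIM measures of the strategy are collected in the two intervention EDs only. Of the three inputs to progression, reach is therefore the only one compared between arms.

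**The concern.** The criteria are open, but strategy effectiveness is already named as one of their inputs. The only between-arm result that the plan will produce for it is a significance test on four randomized units. If the group uses what the plan will hand it, the natural rule is whether reach differed significantly.

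That rule works badly in two different ways. With a valid ED-level analysis, it would usually miss a gain of the size used in the plan's own power statement. With the planned patient-level z-test, it would often endorse a strategy with no effect, because differences between EDs are counted as if they were differences between independent patients. Changing the test alters which error occurs, but the number of EDs stays at four. Progression to the larger trial is a main decision that this pilot is meant to inform.

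**Working it through.** **The plan's own figure.** For 20% against 30%, two-sided alpha 0.05, 80% power and independent patients, the pooled-variance formula gives

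n = [1.96·√(2·0.25·0.75) + 0.842·√(0.20·0.80 + 0.30·0.70)]² / 0.10² ≈ 293.2, so 294 per condition.

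The stated 300 is reproduced at a control reach near 20%, with no allowance for clustering. At 45% against 55% the same formula needs 392. The article states no baseline, so 20% is used below as an assumption.

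**Inputs.**
- From the article: 2 EDs per arm; about 5,000 eligible patients (Effectiveness/reach), so 5,000/4 = 1,250 per ED if equal; a 10-point effect; alpha 0.05 (taken as two-sided).
- Assumed: control reach 20%; between-ED SD of 3, 5 or 8 points, with 1 point as a favourable case. At 20% reach, SD²/(0.20·0.80) gives ICCs of about 0.006, 0.016 and 0.04, and 0.0006 for the favourable case.

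**SE of the difference in mean ED reach.** With two EDs per arm, SE² = (v₀ + v₁)/2, where v = SD² + p(1−p)/1,250.
- The binomial part is 1.28 squared points at 20% and 1.68 at 30%, average 1.48.
- Under a true gain, SE = √(SD² + 1.48). Under no effect, SE = √(SD² + 1.28).

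**ED-level t-test.** It has 2 df and critical value 4.303. Power comes from the noncentral t with noncentrality 10/SE. The median CI half-width is 4.303 · SE · √(ln 2), because the median of chi-square on 2 df divided by 2 is ln 2.

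**Planned z-test when there is no effect.** Its SE is √(2·0.20·0.80/2,500) = 1.13 points, so it declares significance beyond 1.96 · 1.13 = 2.22 points. The chance of a significant result in favour is 1 − Φ(2.22/SE).

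| Between-ED SD (points) | 1 | 3 | 5 | 8 |
|---|---|---|---|---|
| SE, true 10-point gain | 1.57 | 3.24 | 5.15 | 8.09 |
| Noncentrality 10/SE | 6.35 | 3.09 | 1.94 | 1.24 |
| Power, ED-level t-test | 87% | 40% | 21% | 12% |
| Median 95% CI half-width (points) | 5.6 | 11.6 | 18.4 | 29.0 |
| SE, no effect | 1.51 | 3.21 | 5.13 | 8.08 |
| z-test favours a null strategy | 7% | 24% | 33% | 39% |
| Observed gain ≥5 points, true gain 10 | >99% | 94% | 83% | 73% |
| Observed gain ≥5 points, no effect | <1% | 6% | 16% | 27% |

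Simulation of the same model agrees with these values to within a percentage point. It also puts the valid t-test's rate of favouring a null strategy at 2.5%. At an SD of 2 points its power is 61%.

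**Sensitivity to the baseline.** For 15% against 25%, ED-level power is 44%, 29%, 18%, 11% and 8% at ICC 0.005, 0.01, 0.02, 0.05 and 0.10. Across baselines of 5% to 45% it is 7% to 43% at ICC 0.01 to 0.10, and at most 64% at ICC 0.005.

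**Permutation test.** Four EDs can be split 2 and 2 in six ways. The smallest two-sided p is 2/6 = 0.33 even if every split is allowed, so an exact test cannot reach 0.05.

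**The case against.** The strongest objection is that no gate exists yet. A reader might infer that the article already ties progression to the between-arm difference. It does not. Reach is defined as a proportion, effectiveness is weighed jointly with feasibility and acceptability, and nothing says that the z-test result is a criterion. A floor on reach in the intervention EDs would fit the present wording. This stands, and it limits the point to what the criteria should exclude.

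A reader might also infer that two EDs per arm make any rule on the difference useless. The table contradicts that. An illustrative 5-point threshold passes a true 10-point gain in 94%, 83% and 73% of trials, against 6%, 16% and 27% with no effect. At an SD of 3 points that is a usable pilot screen.

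Nor does a valid ED-level test readily advance a useless strategy. It does so in 2.5% of trials, and its weakness is missed effects. False endorsement arises with the patient-level z-test or a point-estimate rule.

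Replacing the comparison with a reach floor alone is not clearly better, because it discards the randomized control and depends on an unknown baseline. If baseline reach were really 30%, a floor of 25% in each intervention ED would pass a strategy with no effect in 88%, 69% and 53% of trials at SDs of 3, 5 and 8 points.

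Finally, the SDs and control reach are assumptions. Controls receive only an information session and flyers, so their reach may be low and vary less. The balance-constrained allocation may also remove some between-ED variation. Both could improve the figures, but the article gives nothing from which to say by how much.

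**Conclusion.** The point holds in limited form. Progression rests partly on strategy effectiveness, and the only between-arm result planned for it is a significance test on 2 against 2 EDs. As a progression criterion, that significance would be unreliable. A valid ED-level test would miss a true 10-point gain in about 60%, 79% and 88% of trials at between-ED SDs of 3, 5 and 8 points. The planned z-test would favour a null strategy in about 24%, 33% and 39%.

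These figures assume 20% control reach, equal EDs of 1,250 patients and normally distributed ED reach. With between-ED SD near 1 point, ED-level power is 87% and the problem largely disappears. The article offers no estimate of that variation, and four EDs cannot estimate it well.

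**What to change.** In the Discussion paragraph on progression, state that neither the p-value nor the statistical significance of the between-arm reach difference will be a progression criterion. In Aim 3, Analysis, report reach for each ED, and the between-arm difference descriptively with an ED-level interval.

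Set the a priori criteria on feasibility and acceptability (FIM and AIM) and on reach achieved in the intervention EDs, read alongside control-ED reach so that a high baseline is not credited to the strategy. If the group wants a point-estimate threshold on the difference, state with it the chance of passing a strategy with no effect and of missing a 10-point gain, over a range of between-ED SDs.

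The cost is a few sentences before the criteria are set, and no new data, since enrolment is already tracked by site. The downside is that the team cannot cite a significant pilot effect as a reason to progress.

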## Data Availability

Not currently applicable. Data from the pilot trial will be available in the NIAAA data sharing archive: https://nda.nih.gov/niaaa/.

## Abbreviations

AUDIT-C: Alcohol Use Disorders Identification Test-Consumption
ED: Emergency department
EHR: Electronic health record
i-PARIHS: Integrated Promoting Action on Research Implementation in Health Services
UAU: Unhealthy alcohol use
